## Abstract

**Background:**

Diabetes is highly prevalent and contributes to significant morbidity and mortality worldwide. Behaviour change interventions that target health and lifestyle factors associated with the onset of diabetes can delay progression to diabetes, but many approaches rely on intensive one-to-one contact by specialists. Health coaching is an approach based on motivational interviewing that can potentially deliver behaviour change interventions by non-specialists at a larger scale. This trial protocol describes a randomized controlled trial (CATFISH) that tests whether a web-enhanced telephone health coaching intervention (IGR3) is more acceptable and efficient than a telephone-only health coaching intervention (IGR2) for people with prediabetes (impaired glucose regulation).

**Methods:**

CATFISH is a two-parallel group, single-centre individually randomized controlled trial. Eligible participants are patients aged ≥18 years with impaired glucose regulation (HbA1c concentration between 42 and 47 mmol/mol), have access to a telephone and home internet and have been referred to an existing telephone health coaching service at Salford Royal NHS Foundation Trust, Salford, UK. Participants who give written informed consent will be randomized remotely (via a clinical trials unit) to either the existing pathway (IGR2) or the new web-enhanced pathway (IGR3) for 9 months. The primary outcome measure is patient acceptability at 9 months, determined using the Client Satisfaction Questionnaire. Secondary outcome measures at 9 months are: cost of delivery of IGR2 and IGR3, mental health, quality of life, patient activation, self-management, weight (kg), HbA1c concentration, and body mass index. All outcome measures will be analyzed on an intention-to-treat basis. A qualitative process evaluation will explore the experiences of participants and providers with a focus on understanding usability of interventions, mechanisms of behaviour change, and impact of context on delivery and user acceptability. Qualitative data will be analyzed using Framework.

**Discussion:**

The CATFISH trial will provide a pragmatic assessment of whether a web-based information technology platform can enhance acceptability of a telephone health coaching intervention for people with prediabetes. The data will prove critical in understanding the role of web applications to improve engagement with evidence-based approaches to preventing diabetes.

**Trial registration:**

ISRCTN16534814. Registered on 7 February 2016.

**Electronic supplementary material:**

The online version of this article (doi:10.1186/s13063-016-1519-6) contains supplementary material, which is available to authorized users.

## Background

Diabetes is a long-term condition characterized by hyperglycaemia in the presence of defects of insulin secretion or insulin action, or both, and is a major cause of morbidity and premature mortality globally [1]. At present, 3.4 million adults in the UK are diagnosed with diabetes, the majority with type 2 diabetes [2]. The damaging effects of uncontrolled hyperglycaemia can cause macrovascular complications (coronary artery disease, peripheral arterial disease and stroke) and microvascular complications (diabetic nephropathy [kidney disease], neuropathy [nerve damage], which can lead to non-traumatic lower limb amputations, and retinopathy, which can lead to blindness) [3]. Altogether, the impact of diabetes is thus significant, with serious implications for health and quality of life, and costs to health care systems. In England, the direct cost to the National Health Service (NHS) of treating type 2 diabetes is approximately £8.8 billion annually, with a further £13 billion associated with indirect costs; these costs are estimated to rise to £15.1 and £20.5 billion, respectively, by 2035–6 [4].

Obesity, physical inactivity and diet are among key risk factors for type 2 diabetes. Weight gain and obesity are especially implicated in the onset of type 2 diabetes. Obese women are nearly 13 times more likely to develop type 2 diabetes than non-obese women; obese men are over 5 times as likely to develop type 2 diabetes [5]. Furthermore, a 1 kg/m^2^ increase in body mass index increases the risk of impaired fasting glucose by 9.5 % [6]. Impaired fasting glucose or impaired glucose tolerance indicate impaired glucose regulation, which is a condition where blood glucose levels are raised, but the levels are insufficient to meet current thresholds for a clinical diagnosis of type 2 diabetes. Impaired fasting glucose is associated with a raised hepatic glucose output, whereas impaired glucose tolerance is associated with peripheral insulin resistance. There is strong and consistent evidence that people with impaired fasting glucose or impaired glucose tolerance have between a 6- and 12-fold risk of developing diabetes, compared with people without, and both are risk factors for fatal and non-fatal cardiovascular events [7].

However, it is well established that lifestyle interventions that target modifiable risk factors such as weight and physical activity can prevent the onset of diabetes in people with impaired glucose regulation. A systematic review of 36 trials showed that diabetes prevention programmes that included diet or physical activity interventions can significantly reduce progression to type 2 diabetes and reduce weight and glucose at 12–18 months, compared with usual care [8]. As such, identification of people with impaired glucose regulation and intervention with lifestyle-change programmes presents significant opportunities for reducing the future incidence of type 2 diabetes. The delivery of these behaviour change interventions is central to guidance from the National Institute for Health and Care Excellence (NICE) on prevention of diabetes in high-risk groups, including people with impaired glucose regulation. However, the delivery of NICE-recommended diabetes prevention programmes is contingent on the availability of specialist staff to provide intensive interventions to relatively small numbers of people over 9 to 18 months. As articulated by the NHS National Diabetes Prevention Programme, the challenge remains to scale up and rapidly roll out evidence-based behaviour change interventions to ensure that more people at risk of diabetes can access to such interventions, but without compromising quality.

### Health coaching

A model of care that has potential to achieve diabetes prevention at a large scale through effective behaviour change is ‘health coaching’. This is a relatively new approach and variously defined but common to this approach is an emphasis on health education and health promotion via patient-centred coaching based on motivational interviewing to improve health outcomes [9].

The increasing adoption of telephone and mobile technologies among patients, and the possibility of delivering care in efficient and flexible ways, has led to significant interest in the potential of telephone health coaching which involves:a regular series of phone calls between patient and health professional… to provide support and encouragement to the patient, and promote healthy behaviours such as treatment control, healthy diet, physical activity and mobility, rehabilitation, and good mental health [10]

However, current evidence of effectiveness is mixed. A systematic review of 13 randomized controlled trials or quasi-experimental studies showed that, in 11 studies, telephone, internet or a combination of telephone, face-to-face, internet or email health coaching can effectively improve physical and mental health, promote healthy behaviours and increase social support among people with long-term conditions [11]. Other reviews have similarly identified a number of effective models, although the important ‘active ingredients’ are not clear [12, 13]. Moreover, much of the evidence is derived from trials conducted in the USA and there is uncertainty about the benefits of health coaching in the UK. A recent evaluation of the nurse-led Birmingham OwnHealth telephone health coaching service for people with long-term conditions (including diabetes) did not find reductions in health service utilization or cost over 12 months [14]. By contrast, a UK trial of telephone support from non-clinical telecare staff (backed up by diabetes specialist nurses) did show significant improvements in glycaemic control in people with type 2 diabetes, compared with usual care [15]. This intervention, now known as Diabetes Care Call, has recently been adapted for use in people with impaired glucose tolerance and impaired glucose regulation. A pilot evaluation (*n* = 44) of the Care Call intervention in people with impaired glucose tolerance showed reductions in weight (2.81 kg, 95 % confidence interval 1.2–4.42), body mass index (1.06 kg/m^2^, 95 % confidence interval 0.49–1.63), and fasting blood glucose (0.29 mmol/l, 95 % confidence interval 0.07–0.51) 1 year after the intervention [16]. Similar outcomes 12 months after the intervention were achieved in a pilot evaluation of Care Call in people with impaired glucose regulation who were offered either a telephone-only or a telephone plus group education pathway [17]. While the findings of these pilot studies are limited by the absence of a control group, they offer proof of concept that telephone health coaching can translate to people with impaired glucose regulation to promote positive and sustained lifestyle changes to prevent type 2 diabetes.

The Impaired Glucose Regulation Care Call intervention has recently been enhanced, with greater use of web-based materials and electronic transfer of patient data, with a view to making the service more engaging for patients, and the provision of care more efficient for providers. The web plus telephone health coaching intervention has been developed by NorthWest EHealth in partnership with Hitachi Europe Ltd. Patient engagement is critical to the success of health promotion interventions and frequent, real-time communication and feedback are key to behaviour change and empowering patients to manage their behaviour [18, 19]. Information technology (IT) platforms, such as desktop applications, mobile short message service (SMS) and internet-based interventions are increasingly used to support and enhance patient engagement in self-management programmes. There is partial evidence that e-health interventions, described as second-generation interactive computerized interventions, can lead to positive improvements in physical activity and diet in people drawn from community and health settings [20] and can also support diabetes self-management tasks [21]. However, the evidence in favour of using IT interventions to support behaviour change is equivocal and few studies have assessed whether satisfaction and usability lead to better engagement and less costly delivery [22].

The addition of an IT platform within the Impaired Glucose Regulation Care Call service might lead to significant advantages in patient uptake and engagement, as well as freed human resources for the provider, which could ultimately improve the clinical effectiveness and cost-effectiveness of the service. However, there is a need to conduct an assessment of satisfaction, usability and cost of delivery of the new web-enabled telephone health coaching service (known as IGR3). This trial will therefore compare user experience and cost of delivery of IGR3 with the existing telephone-only health coaching service (known as IGR2). Further study into the potential impact of the IGR3 model on the clinical and cost effective aspects will then be planned.

## Methods/Design

### Trial design

This trial protocol is written in accordance with standardized reporting guidance from SPIRIT (see Additional file 1) [23, 24].

This trial is a pragmatic, two-arm, patient-level randomized and controlled comparison of two health coaching services, one of which is already commissioned by Salford Clinical Commissioning Group and provided in the NHS by Salford Royal NHS Foundation Trust (i.e. IGR2). As a comparison of ‘active’ interventions, the expected differences in effectiveness are likely to be small, and the trial is not designed primarily to assess differences in clinical outcomes. Therefore, the objective of this trial is primarily to assess the acceptability of IGR3 compared with IGR2, with a secondary aim of examining whether IGR3 will result in a more efficient delivery method.

This trial will test the hypothesis that a web-enhanced telephone health coaching intervention for people with impaired glucose regulation (IGR3) will be more acceptable than an existing telephone-only health coaching intervention (IGR2). We are also going to examine whether IGR3 will provide a more efficient delivery method.

### Primary objective

To assess, quantitatively, whether a web-enhanced telephone coaching intervention (IGR3) is more acceptable than an existing telephone-only coaching intervention (IGR2) for people with impaired glucose regulation.

### Secondary objectives

To determine whether the delivery of the IGR3 intervention is more efficient than the existing commissioned IGR2 while maintaining the quality of service on a similar levelTo explore the cost-effectiveness of IGR3 in comparison with IGR2To explore and compare user and provider experience of IGR3 and IGR2 interventions qualitativelyTo explore the impact, if any, of IGR3 compared with IGR2 on clinical outcomes relevant to diabetes prevention in people with impaired glucose regulation

### Study setting

This trial will be a single-centre study conducted in Salford, UK. Salford is a city in the north west of England made up of eight neighbourhoods with a population of 247,000 (34000 aged 65 and over) and ranked as the 16th most deprived local authority in England out of 326 [25]; approximately 14 % of the adult population are obese [26]. There are 47 general practices in the city, clustered in eight neighbourhoods.

### Interventions

The intervention and control in the trial are both forms of health coaching. Figures 1 and 2 show the care pathways for IGR2 and IGR3, respectively. A comparison of the two services (highlighting their similarities and differences) is shown in Table 1. The key differences between the arms are that IGR3 provides patients with a web desktop dashboard to track progress against patient-centred goals (e.g. weight, dietary modifications) and a pedometer to monitor physical activity. Patients in the IGR3 arm also have access to educational content on the web dashboard in addition to the paper-based educational materials given to patients in the IGR2 arm.

**Fig. 1 Fig1:**
[figure not shown]
Care pathway for IGR2. GP, general practitioner; IGR, impaired glucose regulation

**Fig. 2 Fig2:**
[figure not shown]
Care pathway for IGR3. GP, general practitioner; IGR, impaired glucose regulation

**Table 1 Tab1:** Comparison of intervention characteristics

Comparison	IGR2	IGR3
Materials	Patient information package	Web-based patient tracking system for diabetes specialist nurse
	Educational materials	Web-based patient information, videos and data recording
		SMS
		Patient information package, including pedometer, self-assessment link and log-in details
		Educational materials
Providers	Diabetes specialist nurse or dietician	Diabetes specialist nurse or dietician
	Health advisor	Health advisor
	Administrative support	Administrative support
Modes of delivery	Telephone support	Telephone support with web-based patient tracking
Location of delivery	Remote	Remote
Intervention components		
Triage	Call from diabetes specialist nurse	Call from diabetes specialist nurse
Introduction call	Call from health coach	Call from health coach
Self-assessment	Not applicable	Online self-assessment
Action planning call	Pre-call admin	Pre-call admin
	Call to patient	Call to patient
	Post-call admin	Post-call admin
Tracking	Telephone	Online and telephone
Follow-up calls 1–6	Pre-call admin	Pre-call admin
	Call to patient	Call to patient
	Post-call admin	Post-call admin
Step-down call at 9 months	As follow-up call 1	As follow-up call 1
Tailoring	Content of intervention in response to patient self-evaluation	Content of intervention in response to patient self-evaluation

### Data and outcomes

#### Demographic and clinical characteristics

Data about demographic and clinical characteristics will be entered on a case report form by the researcher at the baseline appointment. We will use sociodemographic questions from the General Practice Patient Survey [27], including sex, age, current work situation and qualifications. Ethnicity will be assessed using the 17 Census 2011 categories [28]. We will include a single-item health literacy measure, which has demonstrated good reliability and validity [29, 30], and a measure of the number and impact of long-term conditions [31].

### Primary outcome measure

#### Patient experience

Patient satisfaction will be assessed using the Client Satisfaction Questionnaire (CSQ-8), which is a generic survey instrument used widely in primary care clinical trials [32]. The CSQ-8 is an eight-item self-administered questionnaire collected at the end of service delivery and scored using a four-point Likert scale. The CSQ-8 scores range from 8 to 32, with higher values indicating higher satisfaction.

### Secondary outcome measures

#### Costs of intervention

The costs of delivery of IGR2 and IGR3 will be determined. Hitachi Europe Ltd, with support from Salford Royal Foundation NHS Trust, will provide a detailed cost breakdown of the operation of IGR2 and IGR3, including staff and infrastructure. Data on number and length of calls for each element of the care pathway in each arm will be recorded throughout the trial period. Clinicians responsible for delivery of the intervention will log call times using a standardized activity log pro-forma.

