### Randomization and allocation concealment

On providing consent, participants will be asked to complete baseline assessments and are then randomized using a remote and automated randomization service provided by the Manchester Academic Health Science Centre Clinical Trials Unit (MAHSC-CTU) at the Christie Hospital NHS Foundation Trust, Manchester, UK. To ensure allocation concealment, randomization will be by means of a computer-generated code implemented by a MAHSC-CTU employee and shared by telephone with the Care Call administrator following correct exchange of a password. The Care Call administrator will communicate allocations to Care Call staff (diabetes specialist nurse and health advisors). Participants will be allocated 1:1 to either IGR2 or IGR3 using minimization to ensure balance for age (<40, 40–60, >60 years) and body mass index (≤18.5, 18.6–24.9, 25.0–29.9). We will use minimization with a probability weighting of 0.75 to reduce predictability.

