### Health economic analysis

The health economic analysis will comprised two parts, both of which will assess the cost-effectiveness of health coaching with a web-based IT platform (IGR3) compared with health coaching alone (IGR2) among people with prediabetes. The first will be an incremental cost-effectiveness analysis from a clinical commissioning group perspective using patient satisfaction and intervention costs to derive a cost per additional unit of patient satisfaction. The second analysis will be conducted from an NHS and personal social services perspective [44]. Costs will include intervention costs and healthcare and social services resource costs. The quantity of resource use will be collected by questionnaire and a set of national average unit costs will be applied (e.g. [45]). The use of the EQ-5D-5 L will enable the estimation of quality-adjusted life years by calculating the area under the curve [46]. An incremental cost-effectiveness ratio (cost per additional quality-adjusted life year) will be used to assess cost-effectiveness of IGR3 in comparison with IGR2. Cost-effectiveness planes and cost-effectiveness acceptability curves will be constructed to reflect any uncertainty in the results and threshold.

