### Access to data and dissemination policy

As the sponsor of the trial, the University of Manchester will remain the custodians of the data collected from participants during the trial and will not share data with any third party, including private companies, without the consent of the participants. Data will not be released to third parties or private companies (including the funder) before the trial has been completed and will be analyzed by an independent evaluation team at the University of Manchester. No interim analysis is planned and no interim data will be shared with the funder or third parties. In recognition of the importance of transparency and need to increase trust in clinical trial results both Hitachi Europe Ltd, and the University of Manchester will agree to data sharing in accordance with proposals outlined by the International Committee of Medical Journal Editors, which state that authors share with others the deidentified individual-patient data underlying the results presented in the trial report (including tables, figures, and appendices or supplementary material) no later than 6 months after publication [59]. Hitachi, as the funder of the trial and as owners of the technology to be tested, may wish to invoke a brief embargo (up to 3 months) on data sharing before publication in an open-access journal.

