Working with industry partners in health services research is novel and presents unique challenges, not least the need to maintain independence. Hitachi Europe Ltd, have invested in the Care Call service at Salford Royal NHS Foundation Trust to improve efficiencies, such as employing an administrator and a research nurse to expedite quality referrals into the service. With the support of the trial steering committee, the CATFISH trial is being run as an independent evaluation and we have ensured that sufficient safeguards are in place to preserve independence throughout all phases of the trial. This includes a commitment to open-access publication and data sharing, in keeping with policies to prevent publication and outcome reporting bias of clinical trials.

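### Delivery costs for both arms come from the funder that owns IGR3, and call times from staff who know the allocation; no stated safeguard covers either input

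*Protocol article*

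**What the plan says.** All references are to the protocol article.

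- **Source of costs.** Costs of intervention states that "Hitachi Europe Ltd, with support from Salford Royal Foundation NHS Trust, will provide a detailed cost breakdown of the operation of IGR2 and IGR3". The breakdown is to cover staff and infrastructure.
- **Source of call times.** The same section adds: "Clinicians responsible for delivery of the intervention will log call times using a standardized activity log pro-forma".
- **Position of the supplier.** Access to data and dissemination policy describes "Hitachi, as the funder of the trial and as owners of the technology to be tested". The Background (Health coaching) says that the web plus telephone intervention "has been developed by NorthWest EHealth in partnership with Hitachi Europe Ltd". IGR2 is a commissioned service provided by the Trust (Trial design).
- **Knowledge of allocation.** Under Randomization and allocation concealment: "The Care Call administrator will communicate allocations to Care Call staff (diabetes specialist nurse and health advisors").
- **Use of the inputs.** Trial design sets the acceptability objective "with a secondary aim of examining whether IGR3 will result in a more efficient delivery method", and efficiency is the first of the Secondary objectives. Under Health economic analysis, the first evaluation works by "using patient satisfaction and intervention costs to derive a cost per additional unit of patient satisfaction". The second adds health and social care costs to the intervention costs.
- **Independence.** The Discussion says that "we have ensured that sufficient safeguards are in place to preserve independence throughout all phases of the trial".

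**The concern.** The party with a commercial interest in IGR3 supplies the costs of IGR3 and also those of the service it is compared with. The other main input, staff time on calls, is recorded by people who know which service they are delivering.

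The article also publishes the direction that it expects. The Background hopes that the IT platform will release staff time, and the theory of change under Qualitative study predicts lower delivery costs with IGR3.

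At stake is the answer to whether IGR3 is cheaper to deliver. A biased unit cost or a log that differs by arm would pass straight into the cost difference. Independent analysis downstream could not remove it.

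**Working it through.** The article gives no figure for delivery cost, so there is nothing to reproduce. The check traces the inputs through the text and then sizes one of them.

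**Step 1: where the inputs go.**

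| Analysis | Role of intervention cost |
|---|---|
| Efficiency aim (Trial design, Secondary objectives) | Determines the answer |
| Cost per unit of satisfaction, commissioner perspective (Health economic analysis) | Only cost term |
| Cost per QALY, NHS and social services perspective (same section) | One component, beside health and social care use from questionnaire (and record linkage, Health resources usage) |
| CSQ-8 primary comparison (Statistical analysis) | None |

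**Step 2: what the stated safeguards cover.**

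| Stated safeguard | Section | Covers the cost breakdown or call logs? |
|---|---|---|
| Steering committee support | Discussion | Not stated |
| Open publication and sharing of data | Discussion | No; acts after the inputs are fixed |
| Analysis by an independent university team | Access to data and dissemination policy | Covers analysis, not supply of inputs |
| No interim data to the funder | Access to data and dissemination policy | No; concerns data leaving the trial |
| Blinding of research team and statistician | Blinding | No; the health economist is unblinded and delivery staff know the arm |

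No row describes verification of the breakdown or of the logs.

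**Step 3: how many calls can be logged with knowledge of the arm.** Table 1 lists triage, introduction, action planning, six follow-up calls and a step-down call: 1 + 1 + 1 + 6 + 1 = 10. Recruitment to the trial places triage before the trial administrator's first contact, and randomization follows consent and baseline assessment. Triage cannot be logged with knowledge of the arm, so 10 − 1 = 9 calls are exposed.

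**Step 4: illustrative size.** The article gives neither call length nor logging error. Both are assumptions here: 20–30 minutes per call and a 10% difference in logging between arms.

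- Per patient: 9 × 20 × 0.10 = 18 minutes; 9 × 30 × 0.10 = 27 minutes.
- Per 100 patients (the planned arm size): 18 × 100 / 60 = 30 hours; 27 × 100 / 60 = 45 hours.

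With an assumed fixed error per call instead, 1, 2 or 5 minutes gives 9, 18 or 45 minutes per patient, that is 15, 30 or 75 hours per 100 patients.

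These are sizes without a direction: nothing in the article shows which arm would be over-recorded. They cannot be turned into money or set against an expected saving, because the article gives neither a unit cost nor a target difference.

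**The case against.** The case against is substantial, and much of it stands.

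- **Independence.** A reader might infer that the article contradicts itself. It does not. Independence is claimed for evaluation, analysis and release of data; nowhere does it say that cost inputs come from a disinterested party. The list of safeguards in the Discussion is also not presented as complete.
- **No check at all.** A reader might infer that nobody will verify the costs. The article is condensed, and audit of unit costs commonly sits in a fuller document. What can be said is that none is stated. The Trust supports the breakdown and the log form is standardized, which are partial mitigations.
- **Pricing of staff time.** A reader might infer that national unit costs are withheld from intervention staff. The Health economic analysis ties national unit costs to questionnaire-based resource use and is silent on intervention staff. Actual local costs are also defensible from a commissioner's perspective.
- **Motive and blinding.** Delivery staff cannot be blinded, and no interest of theirs in the result is shown. The funder's employees named in the Discussion are an administrator and a research nurse, not the coaches.
- **Limits of any remedy.** No section says that system call records exist. Such records would not measure the pre-call and post-call administration in Table 1. The trial was already in follow-up (Trial status), so some logging was done. Platform prices must still come from the owner.

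One point is not answered: the article does more than omit a check. It positively assigns the costing of both arms, including the comparator run by another body, to the interested party. That is a stated choice of data source, not a detail left for elsewhere.

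**Conclusion.** The point holds as an unguarded source of bias in the secondary efficiency and cost-effectiveness results. It reaches the whole cost term of the commissioner-perspective analysis and part of the cost term of the other. The primary result is untouched.

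The 30–45 staff hours per 100 patients are an illustration that rests wholly on the assumed call length and the assumed 10% differential; they do not estimate an actual error. The stronger reading, that a finding in favour of IGR3 would simply not be credible, goes too far: bias is possible and unguarded on the stated text, but it is not shown. The change is worth making because it is cheap and protects a result in which the funder has an interest.

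**What to change.** Revise Costs of intervention as follows:

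1. The trial health economist builds the intervention costs for both arms, with one common set of staff unit costs. Whether these are national or local is a choice to state and justify.
2. The Trust supplies the IGR2 running costs.
3. The funder supplies only documented IGR3 platform, hosting, SMS and pedometer prices.
4. Logged call times in both arms are checked against system call records where the Trust holds them. Where it does not, say so and keep the logs as the source.
5. Funder-supplied prices and logged times are varied in sensitivity analysis, over ranges set before costs are compared by arm.

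The breakdown is still described as something to be provided, so this remains possible during follow-up. It needs no new participant data and leaves both services as they are. The cost is a data request to the Trust and some extra work by the existing health economist. Logs already completed cannot be redone, which is a further reason for the sensitivity analysis on logged times.
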